### Additional consent provisions for collection and use of participant data and biological specimens {26b}

Adolescents will be informed that they may withdraw their consent at any moment, while highlighting that data collected up to the point of withdrawal will be used for the study. In addition, they will be asked to give permission to access their data for the purpose of monitoring, by other people from the research team and regulatory authorities that are mentioned in the information letter. Adolescents are also asked if their coded data may be used in follow-up research and if they may be contacted for future research related to this study. Through the consent form, they (and both parents if the adolescent is under [16]) provide their consent for these conditions. This study does not involve the collection of biological specimens.

### Interventions

#### Explanation for the choice of comparators {6b}

To investigate the effectiveness of early intervention for BPD symptoms in adolescents with presenting depression, anxiety, or both and emerging BPD, CBT for depression and anxiety will be compared to MBT-early. CBT is currently offered as the first-choice psychological treatment for adolescents with presenting symptoms of depression and anxiety, according to the Dutch treatment guidelines [37], following a stepped care approach, where the presenting symptoms of depression and anxiety are typically addressed first, even in the presence of underlying BPD symptoms. Hence, CBT is an appropriate comparative treatment option in the current study as it is currently typically offered to these young people in the Netherlands.

#### Intervention description {11a}

##### CBT

CBT [38] is a psychotherapeutic intervention that adolescents with presenting symptoms of depressive and anxiety disorders receive according to the Dutch treatment guidelines [37] as a first-choice psychological treatment. CBT is an evidence-based, goal-directed approach utilizing cognitive restructuring and behavioural interventions. This therapeutic model aims to identify and modify maladaptive thought patterns and behaviours, equipping individuals with practical coping skills to mitigate symptoms and enhance overall emotional resilience. In this study, CBT is offered as an individual treatment following a manualized treatment protocol [39]. The treatment consists of an average duration of 12–16 sessions, encompassing assessment and case formulation, a treatment phase, and a closure phase. Additionally, post-treatment relapse prevention booster sessions may be offered within the first 3 months after treatment.

**Assessment and case formulation**

This initial phase involves the assessment of the adolescent’s issues and the formulation of a case conceptualization to identify specific problems and tailor treatment accordingly (2–3 sessions). Collaboratively, the therapist and the adolescent establish goals such as symptom reduction, coping skills development, and improvement in daily functioning.

**Treatment phase**

The next phase of treatment involves interventions such as psychoeducation, teaching coping strategies (breathing and relaxation techniques, problem-solving skills, and distraction techniques), cognitive restructuring (addressing automatic negative thoughts), and exposure exercises (involving gradual exposure to fearful objects or situations), as well as strengthening coping skills and activation (enhancing daily structure such as attending school, engaging in hobbies, and participating in social activities to counteract passive behaviour and avoidance associated with depression) aimed at improving depressive and anxiety symptoms. Parents are provided with information regarding the adolescent’s presenting symptoms and the treatment plan. They are asked to actively engage in facilitating and executing exposure exercises. Additionally, supplementary supportive interventions for parents may be added, if needed [39].

**Closure phase**

This phase is aimed at reinforcing and maintaining the skills learned during therapy, preventing potential relapse or setbacks. Sessions focus on the evaluation of the treatment gains in relation to the predetermined goals and teaching of relapse prevention (2–3 sessions). Booster sessions involve additional sessions or follow-up sessions scheduled within the first 3 months after treatment completion (2–4 sessions). The booster sessions aim to consolidate progress, address any emerging issues, and fine-tune strategies to ensure the sustained effectiveness of the treatment over time.

##### MBT-early

MBT was originally developed as an intervention for adults with BPD. Several types of MBT for BPD are empirically supported [40–42]. MBT-early, developed at de Viersprong and implemented since 2014, has offered preliminary support from a small naturalistic pilot study [43].

The aim of MBT-early is to improve the capacity for mentalizing and social learning (i.e. epistemic trust). Impairments in these fundamental capacities are assumed to underly psychopathology [44]. MBT-early aims to facilitate adolescents and their parents to better understand their own and others’ thoughts, feelings, intentions, and motivations and to foster epistemic trust, i.e. nurturing confidence in one’s own perceptions and beliefs, as well as developing trust in others’ perspectives.

MBT treatment programmes vary in terms of treatment components, duration, and intensity. MBT-early shares with all other MBT programmes that it is highly structured and systemically planned. The three C’s, consistency, constancy, and coherence, form a foundational principle for all MBT treatment programmes (see a detailed description elsewhere, [45]) and thus for MBT-early.

MBT-early is a time-limited specialized treatment for emerging BPD and comprises two phases: an initial intensive treatment phase of 16 weeks, followed by a 6-month booster treatment phase.

**Intensive treatment phase**

The intensive treatment phase consists of an assessment phase (3–4 sessions), a middle phase (10 sessions), and a final phase (2 sessions). The sessions include 16 individual sessions, 3 family sessions, 2 treatment review sessions, and, if necessary, psychiatric consultations and case management (e.g. consultation with school). These treatment modalities are delivered by 1 therapist, and interventions are tailored to the specific needs of the adolescent and his/her family (e.g. case management may partially replace individual sessions if problems manifest primarily at school). However, this standard package can be downscaled in cases of rapid improvement or upscaled when needed.

**Booster treatment phase**

The intensive treatment phase is followed by a booster phase with follow-up sessions 1, 2, 4, and 6 months after the end of the first phase. At the final session, the treatment progress is assessed to determine if the therapy can conclude or if a new phase of care is necessary. Additional care can be provided in consultation with the family and the treatment team, even after the closure of the adolescent’s case.

##### Criteria for discontinuing or modifying allocated interventions {11b}

Adolescents can withdraw from the study at any time for any reason if they wish to do so without any consequences for their treatment, i.e. they can complete their current assigned treatment (either MBT-early or CBT), but will not be contacted for further assessments. Previously collected data will be included in the analyses.

The research team will register and follow up all potential serious adverse events (SAEs) that might be associated with the treatment (e.g. suicide), which may ultimately lead to the ending of the study. These SAEs will also be reported and discussed at a trial steering committee (TSC). The TSC may decide to end the study prematurely if a significant difference in SAEs (> 5) is shown between the two treatment conditions. For more details on the SAEs, see ‘Adverse event reporting and harms {22}’ section.

##### Strategies to improve adherence to interventions {11c}

Both the CBT and MBT-early teams consist of therapists with broadly ranging level of experience, background, and educational level. All therapists involved in the study are certified psychologists, sociotherapists, remedial educationalists, or psychotherapists. Clinicians within the CBT teams who are involved in the study have successfully completed a certified CBT basic course or are further trained in CBT. CBT therapists have weekly one-on-one supervision to review case material with their supervisor. MBT-early therapists who are involved in the study have successfully completed a certified MBT basic course at the minimum or are further trained in MBT. Within the MBT-early programme, biweekly team supervision focuses on reviewing case material to increase therapists’ comprehension of mentalizing theory and their competency in working with the principles of MBT and the spectrum of mentalizing interventions. In order to test for adherence, ten randomly selected individual sessions of both CBT as well as the MBT-early will be scored on an, for the treatment appropriate, adherence scale.

##### Relevant concomitant care permitted or prohibited during the trial {11d}

By default, no other interventions will take place during the intensive phase of treatment. However, when it is deemed clinically necessary to add other psychological interventions, concomitant care can be offered within the same mental healthcare institution as the assigned treatment or somewhere else.

##### Provisions for post-trial care {30}

Throughout the treatment, the mental health professional will, in collaboration with the adolescent, evaluate whether the allocated treatment is sufficiently beneficial or if an alternative treatment might be more appropriate, either within the same mental healthcare institution or elsewhere. After dropping out or completing the allocated treatment, participants can also receive the non-assigned treatment (e.g. receiving MBT-early after completing CBT or vice versa). Based on the intention-to-treat principle, adolescents dropping out of the allocated treatment will be followed for research purposes, unless they withdraw their consent to participate in the follow-up assessments.

The sponsor has a liability insurance which is in accordance with Article 7 of the WMO (Medical Research Involving Human Subjects Act; in Dutch: Wet Medisch-wetenschappelijk Onderzoek met Mensen [WMO]). The risks of participating in this study are minimal. The interviews and assessments may be somewhat burdensome but do not carry specific risks. For this reason, the sponsor is dispensed from the obligation to provide insurance for participating in medical research by the Medical Research Ethics Committee (in Dutch: medisch-ethische toetsingscommissie [METC]) of the Erasmus Medical Center (MC).

### Outcomes {12}

Table 1 presents an overview of the time points for each outcome measure.

**Table 1 Tab1:** Time point of each outcome measure

	**Measures**			**Assessment**				
	**Measure**	**Respondent**	**Type**	**Baseline**	**End of treatment**	**12-month follow-up**	**18-month follow-up**	**24-month follow-up**
Severity of BPD	BPDSI-IV-ado	A	Interview	x	x			x
Severity of depression and anxiety	PHQ-9^a^	A	Questionnaire	x	x	x	x	x
	GAD-7^a^	A	Questionnaire	x	x	x	x	x
	C-SSRS^a^	A	Interview	x	x			x
	BSI	A	Questionnaire	x	x	x	x	x
	CBCL	P	Questionnaire	x	x	x	x	x
Personality functioning	LPFS-BF 2.0^a^	A	Questionnaire	x	x	x	x	x
	RFQ-8	A	Questionnaire	x	x	x	x	x
Social functioning	WHODAS 2.0^a^	A	Questionnaire	x	x	x	x	x
	KIDSCREEN-10^a^	A	Questionnaire	x	x	x	x	x
	EQ-5D-NL	A	Questionnaire	x	x	x	x	x
	NRS-BSV	A	Questionnaire	x	x	x	x	x
Academic functioning	School attendance	A	Questionnaire	x	x	x	x	x
Economic evaluation	TiC-P	P	Questionnaire		x	x	x	x
	Questions about extra time investment treatment	P	Questionnaire		x	x	x	x
Demographic variables	Questions about living situation, nationality, level of education, current school, and/or work status	A	Questionnaire	x				

^a^Recommended by ICHOM

#### Primary outcome

##### Severity of BPD symptoms

The primary outcome variable is the reduction in severity of BPD symptoms from baseline to end of treatment assessed using the Borderline Personality Disorder Symptom Severity Index for Adolescents (BPDSI-IV-ado). The BPDSI-IV-ado is a semi-structured interview to assess the severity of BPD symptoms in adolescents and to detect short-term changes [46]. The BPDSI-IV-ado consists of 72 questions, spread over the 9 criteria for BPD. The total scale ranges from 0 to 90, and the subscales range from 0 to 10. The interview is designed to obtain detailed scores for each BPD symptom and to assess the severity of BPD symptoms over the past 3 months. The internal consistency of the BPDSI-IV-ado is moderate to high (Cronbach’s *α* ranging from 0.62 to 0.94) and the BPDSI-IV-ado has been demonstrated to be a reliable and valid instrument for the assessment of the severity of borderline symptoms in adolescents [46].

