## Statistical methods

### Statistical methods for primary and secondary outcomes {20a}

Data analysis will be conducted using SPSS Statistics. Treatment outcomes of the primary outcome, severity of BPD symptoms, over time will be examined using multilevel modelling. Multilevel modelling is able to model data from different time points, correcting for the dependency of observations by adding a within-subject correlation structure to the regression model. Another advantage of multilevel modelling is that it is able to handle missing data, by using the available data irrespective of the number of repeated measurements. In other words, adolescents with an incomplete number of follow-up measurements are also included in the treatment outcome analyses.

The interventions will be compared with the intention-to-treat adolescent sample, that is, with all adolescents randomized to either MBT-early or CBT.

A deviance test using restricted maximum likelihood will be used to assess whether random or fixed slopes should be assumed in models for each outcome variable. Subsequently, time will be included as appropriate (i.e. linear, logarithmic) and included in the model together with the treatment group and time by group interactions if likelihood ratio tests show significant improvement. The primary effect size of the treatments will be estimated from baseline to end of treatment and secondary effect sizes from baseline to 12-, 18-, and 24-month follow-up. Additional treatment offered in the follow-up period will be included as a covariate in the estimation of the multilevel models and effect sizes from baseline to 12-, 18-, and 24-month follow-up, as well as a predictor of treatment outcomes at 12-, 18-, and 24-month follow-up.

The secondary outcomes will be analysed similarly using multilevel modelling, in which the type of model is adapted to the outcome if needed (i.e. binary in case of the C-SSRS) from baseline to end of treatment, 12-, 18-, and 24-month follow-up. As noted, additional treatment offered in the follow-up period will be included as a covariate in the estimation of the multilevel models and effect sizes from baseline to 12-, 18-, and 24-month follow-up, as well as a predictor of treatment outcomes at 12-, 18-, and 24-month follow-up.

To examine the possible influence of missing data, we will repeat the analyses described using datasets in which missing data are imputed with state-of-the-art data imputation methods [66].

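### The primary BPDSI interview is tied to an end of treatment that the visible text does not date and that depends on arm: about 6–7 months later in MBT-early on the literal wording, within a range of 0 to about 7 months

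*Protocol article*

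**What the plan says.** **Primary endpoint.** Under Severity of BPD symptoms: "The primary outcome variable is the reduction in severity of BPD symptoms from baseline to end of treatment". The statistical methods section {20a} uses the same window: "The primary effect size of the treatments will be estimated from baseline to end of treatment". Table 1 gives the later visits in months (12, 18, 24) but names the primary visit only by the event.

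**MBT-early.** The programme "comprises two phases: an initial intensive treatment phase of 16 weeks, followed by a 6-month booster treatment phase". The booster phase has "follow-up sessions 1, 2, 4, and 6 months after the end of the first phase", and the last of these sessions is where it is decided whether therapy can stop. The Intensive treatment phase section lets the package be cut back when improvement is rapid and extended when needed.

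**CBT.** "The treatment consists of an average duration of 12–16 sessions", with no session frequency given. The CBT section calls the optional boosters post-treatment. The Closure phase section describes them among the closing work, yet as "follow-up sessions scheduled within the first 3 months after treatment completion".

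**BPDSI-IV-ado.** The interview is meant to "assess the severity of BPD symptoms over the past 3 months". Table 1 and section {18a} place it at baseline, end of treatment and 24 months only.

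**The concern.** A between-arm difference in change from baseline measures a treatment effect only if both arms have had the same time to change. Here the clock stops at an event whose date depends on the arm. The wording is also asymmetric: the MBT-early boosters are named a treatment phase, while the CBT boosters come after treatment. If the interviews follow that wording, any symptom change that would occur with time alone, under either treatment, enters the primary contrast.

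Two features aggravate this. First, MBT-early length can vary with response, so timing within that arm may depend on the outcome. Second, the 3-month recall window would sit at different stages of care. Weekly CBT ending at 2.8–3.7 months would have most or all of active therapy inside the window. MBT-early ending at 9.7 months would have only months 6.7–9.7 inside it, a period starting about 3 months after the intensive phase.

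No common-time BPDSI before 24 months is available to check the result. By 24 months, participants may have received the other treatment (Provisions for post-trial care).

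**Working it through.** **Inputs.** MBT-early: 16 weeks, then 6 months. CBT: 12–16 sessions, with a booster window of 3 months. Session frequency is not stated, so weekly and fortnightly are both taken as assumptions. One month = 4.348 weeks. From Sample size {14}: d = 0.50, two-sided α = 0.05, r = 0.50, 59 evaluable per group.

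**The plan's own figures.** The article gives no figure for visit timing, so there is none to reproduce. The attrition step does reproduce: 59/0.90 = 65.6, so 66 per group and 132 in total. The 59 is used below only as the stated number analysed. A two-sample or change-score formula gives 2 × (1.960 + 0.842)²/0.50² = 62.8, i.e. 63. Baseline adjustment (factor 1 − r² = 0.75) gives 48. That mismatch is a separate matter and nothing here depends on it.

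**Step 1: programme lengths.**
- MBT-early, intensive phase only: 16/4.348 = 3.7 months.
- MBT-early, both phases: 3.7 + 6 = 9.7 months.
- CBT weekly: 12/4.348 = 2.8 to 16/4.348 = 3.7 months; with the booster window, 5.8–6.7.
- CBT fortnightly: 5.5–7.4 months.

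**Step 2: gap in end of treatment, MBT-early minus CBT.**

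| Reading | CBT frequency (assumed) | Gap, months |
|---|---|---|
| MBT-early both phases; CBT without boosters (literal wording) | weekly | 6.0 to 6.9 |
| Same | fortnightly | 2.3 to 4.2 |
| Boosters counted in both arms | weekly | 3.0 to 3.9 |
| Boosters counted in neither arm | weekly | 0 to 0.9 |

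With fortnightly CBT and boosters counted in neither arm, the order reverses and CBT ends 1.8–3.7 months later.

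**Step 3: what a gap could do.** The documents give no rate of change over time, so the rate is an assumption. Spurious d = gap × shared change per month. With r = 0.50 the SD of a change score is √(2(1 − 0.5)) = 1 times the SD of a single score, so the scale is the same. The standard error at 59 per arm is √(2/59) = 0.184. With no true effect, the two-sided rejection rate is Φ(−1.96 + d/0.184) + Φ(−1.96 − d/0.184).

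| Gap | Change per month (assumed) | Spurious d | Two-sided false-positive rate |
|---|---|---|---|
| 6 months | 0.02 SD | 0.12 | 0.10 |
| 6 months | 0.04 SD | 0.24 | 0.26 |
| 3 months | 0.02 SD | 0.06 | 0.06 |
| 3 months | 0.04 SD | 0.12 | 0.10 |
| 0 | any | 0 | 0.05 |

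A spurious d of 0.12–0.24 is 24–48% of the planned 0.50. If symptoms improve with time, it favours the arm seen later. If they relapse, the sign flips and the size is the same.

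**The case against.** The strongest reply is that the gap may not exist. No section says that the MBT-early interview waits for the booster phase. The boosters there are described as follow-up sessions, and the concomitant-care section ties its default bar on other interventions to the intensive phase alone. Sixteen weeks against 12–16 weekly sessions leaves at most 0.9 months. Figure 1, the participant timeline, is not shown, and the article condenses a fuller protocol in which visit windows may be set. A post-treatment comparison is also a recognised choice for psychotherapies of different length.

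Much of this stands. A reader might infer four stronger claims that the documents do not support:
- **That the gap is six months.** This is one reading, near the upper end of the range.
- **That the bias favours MBT-early.** The Background describes remission and relapse in adult BPD, and cites a primary-care study in which 45%, 60% and 69% of young patients with BPD symptoms made no progress or deteriorated on three outcomes. A later interview could equally work against MBT-early.
- **That dropouts are interviewed earlier.** The article says they are still followed and does not say when. The 40–50% dropout figure comes from cited literature and is not this trial's expectation.
- **That timing reveals the arm to the blinded assessors.** It might cue them if the gap is large, but they are asked to name the allocation after each assessment, so loss of blinding would be recorded.

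The reply does not remove the core. The primary time point is fixed by an arm-dependent event, and the literal wording points to the largest gap. The planned multilevel model still takes its primary effect to end of treatment.

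**Conclusion.** The point holds as a defect in how the primary time point is fixed. It does not show that the primary result is confounded. With weekly CBT, the interview falls between 0 and about 7 months later in MBT-early: 6.0–6.9 on the literal wording, 3.0–3.9 with boosters in both arms, and 0–0.9 with boosters in neither. Fortnightly CBT on the literal reading gives 2.3–4.2. Any gap mixes treatment with elapsed time, and no BPDSI before 24 months can separate them. The illustrated cost is a false-positive rate of 0.10–0.26 for a 6-month gap or 0.06–0.10 for 3 months. It rests wholly on the assumed 0.02–0.04 SD per month, and its direction is open. If Figure 1 or the full protocol already sets one date for both arms, the planned gap is zero and only the article's wording needs correcting.

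**What to change.** 1. Reconcile the CBT, Closure phase, MBT-early and Booster treatment phase sections on which phase closes treatment for assessment purposes. This concerns the visit definition only and leaves the programmes as they are.
2. Set the primary BPDSI interview at one stated time from randomisation, with a window, identical in both arms and applied to dropouts. Date the 12-, 18- and 24-month visits from randomisation as well.
3. For participants already interviewed, report actual time from randomisation by arm. Repeat the multilevel analysis with actual assessment time as a sensitivity analysis, and report the 24-month BPDSI as a same-clock comparison, provided that visit is dated from randomisation.

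**Cost.** A protocol amendment, with no extra interviews and no change in the stated sample size. With a common time, the planned gap and the spurious d from a shared trend are both zero.

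**Downsides.** A common time late enough to follow both programmes may include crossover, since those who finish CBT can then receive MBT-early. Enrolment began in August 2021 and recruitment was due to finish in the third quarter of 2024, so a mid-trial change mixes old and new timings. If most interviews are already done, step 3 is the main remedy left. It is weaker: with one post-baseline BPDSI before 24 months, arm and interview time may nearly coincide, and the adjustment then leans on the assumed shape of change over time.
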